During visits 1, and visit 3, dietary intake data will be collected using a self-administered 2-day 24-h dietary record. All the participants will also be given comprehensive verbal instructions on the method of recording food intake using the 2-day 24-h dietary record. The illiterate participants will be asked to seek assistance from their family members to record for them. They will be asked to complete the 2-day 24-h dietary record of food intake before their next visit, which will be used as the basis for their individualized dietary advice.

During the baseline visit, all data collection will be conducted including a socio-demographic questionnaire, with exception of data for *length of hospital stay* which can only be obtained at visit 2. Meanwhile, anthropometric measurements (except height) and PG-SGA questionnaire, the same methods and instruments will be used repeatedly at visit 1 and visit 3. Data for handgrip will be conducted at every visit while biochemical data will be collected for a second time at the end of the study which is during visit 3. The details of the assessment and procedure are shown in Table 3.

**Table 3 Tab3:** The assessment procedure at (baseline), visit 1, visit 2, and visit 3

The assessment procedure	Visit			
	Baseline	1	2	3

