### Primary outcome measure

#### Length of hospital stay

Length of hospital stay will be recorded starting from postoperative day 1 until the day of the patient’s discharge. The total length of hospital stay will be taken during visit 2, the day of the patient’s discharge.

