### Analysis of results

The data collected will be analyzed by using the statistical software Statistical Package for Social Sciences (SPSS) and checked for normality via Kolmogorov-Smirnov analysis. All data will be normally distributed as indicated by *p*>0.05 unless otherwise stated. If the data will be not normally distributed, analyses will be carried out on the natural logarithm of the values to improve the symmetry and homoscedasticity of the distribution.

Descriptive statistics, including percentages, mean values, and standard deviations, will be used to describe the baseline demographic data, type of diseases, nutritional status level including anthropometric data, and dietary intake. The median will be used when the data are skewed. When the data become skewed, the mean loses its ability to provide the best central location for the data because the skewed data are dragging it away from the typical values. In addition, the median is not strongly influenced by skewed values.

The values from both groups will be compared using an ANOVA test for approximately normally distributed data, followed by tests on pairs of groups using the Bonferroni adjustment. Non-normal data will be compared by the Kruskal-Wallis test followed by the Mann-Whitney *U* test. ANCOVA or logistic regression will be used with models adjusted according to potential confounders to determine predictors of changes in the key outcome variables of the length of hospital stay with *p*<0.05 significance level. An intent-to-treat (ITT) analysis will be performed to determine the effect of the intervention study on the assumption that participants have adhered to the dietary advice and ONS at the start of the intervention study and had baseline and endpoint values. In other words, ITT analysis includes every randomized subject; according to randomized treatment assignment regardless of their non-compliance, subsequent withdrawal from treatment, or deviation from the protocol and anything that happens after randomization. The effect of intervention between treatment groups on outcome parameters will be carried out by using General Linear Model (GLM) for repeated measure procedure. This method is quite robust to violation of the assumption of normality [33].

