A partial Eta-squared measure will be used to compare the magnitude of changes with the large effect size, indicating a significant difference in magnitude [34]. Using Cohen’s classification, the value of partial Eta-squared is considered to be a small effect size at 0.01, a moderate effect size at 0.06, and a large effect size at 0.14 [35].

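### Length of stay is measured once, but the intervention effect is assigned to a repeated-measures GLM that cannot be fitted to it, and the fallback rules leave the primary test and estimand open

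*Protocol article*

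**What the plan says.** All references are to the protocol article.

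- **Outcome.** LOS is primary in the Abstract, in Primary objective and in Primary outcome measure. It runs from postoperative day 1 to discharge, and "The total length of hospital stay will be taken during visit 2". Data collection procedure excepts it from the baseline data as something "which can only be obtained at visit 2". Table 3 marks LOS at visit 2 only.
- **Effect analysis.** Analysis of results: "The effect of intervention between treatment groups on outcome parameters will be carried out by using General Linear Model (GLM) for repeated measure procedure". The Abstract (Methods) names the same procedure shortly after naming LOS as primary. Neither place excepts LOS.
- **If data are normal.** Normality is judged by Kolmogorov-Smirnov at p>0.05. The groups are then compared by ANOVA, with Bonferroni-adjusted pairwise tests.
- **If data are not normal.** One sentence says "analyses will be carried out on the natural logarithm of the values". A later one says "Non-normal data will be compared by the Kruskal-Wallis test", followed by Mann-Whitney. The section then adds that the GLM is robust to non-normality.
- **The only model that names LOS.** "ANCOVA or logistic regression will be used with models adjusted according to potential confounders", to find predictors of changes in LOS.
- **Planning basis.** Sample size calculation uses a between-group difference in LOS of 3.45 days and a standardised effect of 0.8, giving 34 per group.

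**The concern.** A repeated-measures GLM tests a within-subject factor and its interaction with group. LOS has no baseline and no second value, so the one method the article assigns to the intervention effect has nothing to work on for the primary outcome. The analyst must go elsewhere in the section, and what is found there does not settle the matter. Skewed data are to be log-transformed, or ranked, or left as they are because the GLM is robust. The only model tied to LOS by name concerns changes in it, although a single value has no change, and it offers logistic regression with no dichotomy of LOS defined.

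LOS is usually right-skewed, so the non-normal branch is likely to be the one that matters. The candidate methods answer different questions: a difference in mean days, a ratio of geometric means, or a shift in ranks. If the choice is made after LOS has been seen by group, the reported p-value loses its nominal meaning and readers cannot tell which effect the trial set out to estimate.

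**Working it through.** **1. What the planning figure rests on.** Inputs from Sample size calculation: difference 3.45 days, standardised effect d = 0.8, power 90%, α = 0.05 (sidedness not stated), drop-out 20%, 34 per group.

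- Implied SD = 3.45/0.8 = 4.31 days.
- One-sided, normal approximation: n = 2(1.645 + 1.282)²/0.8² = 26.8, so 27 per group; 27/(1 − 0.20) = 33.75, so 34 per group and 68 in total. This matches the article.
- Two-sided t-test: 34 per group before any drop-out allowance, which also gives 68.

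Both routes are for two independent groups with one LOS value each. The sample size therefore assumes a simple two-group comparison in days, not a repeated-measures model. Which route was used is a separate matter.

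**2. Which stated methods can be run on LOS.**

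| Method in Analysis of results | Runs on one LOS value per patient? | Quantity addressed |
|---|---|---|
| Repeated-measures GLM | No: no within-subject factor, no group-by-time term | none |
| ANOVA (with two groups, the t-test) | Yes | difference in mean days |
| Analysis of log values | Yes | geometric-mean ratio |
| Kruskal-Wallis, then Mann-Whitney (with two groups, essentially one test) | Yes | rank shift |
| ANCOVA for predictors of change | Only as an adjusted model of LOS itself; there is no baseline LOS and no change | adjusted difference in mean days |
| Logistic regression for predictors of change | Not without a cut-point for LOS, and none is given | undefined |

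After removing duplicates, three unadjusted group comparisons remain: t, log-t and Mann-Whitney. The Kolmogorov-Smirnov result separates the first from the other two. Nothing separates log-t from Mann-Whitney.

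**3. What the open choice could cost.** The article gives no LOS distribution, so this rests on an assumption: LOS lognormal, SD 4.31, control mean 8, 10 or 12 days, 34 per group, two-sided 5%. The log-scale SD is √ln(1 + (4.31/mean)²), which is 0.505, 0.413 and 0.349. With 20,000 simulated trials per setting:

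| Control mean (days) | t | log-t | Mann-Whitney | At least one p<0.05, no true effect | Tests disagree, true difference 3.45 days |
|---|---|---|---|---|---|
| 8 | 5.0% | 5.3% | 4.9% | 7.2% | 11% |
| 10 | 4.9% | 5.2% | 5.0% | 6.9% | 10% |
| 12 | 5.0% | 5.1% | 5.0% | 6.8% | 9% |

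Other runs under the same assumptions, with fewer replicates, gave 6.0 to 6.8% for the fifth column. Runs with median 8 days, log-SD 0.4 to 0.8 and 27 to 34 per group gave 6.6 to 7.2%. In all of these runs each test alone stayed close to 5% (3.9 to 5.3%). So the cost is 1 to 2 percentage points of type I error if the best of three is picked. With a real effect of the planned size, about one trial in ten would have a significance verdict that depends on the method chosen.

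**The case against.** **The section does contain a runnable comparison.** The ANOVA or Kruskal-Wallis/Mann-Whitney sentence can be applied to LOS. The GLM sentence may have been meant for the secondary outcomes, which are measured at several visits; the Abstract mentions changes in biochemical, nutritional and functional status just before it. A reader might infer that the plan has no usable primary test at all. The documents do not support that. What stands is that the restriction to repeated outcomes is nowhere stated, and that even with it the log and rank rules for skewed data still compete.

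**The rules are not strictly incompatible.** Transforming first and ranking only if skew persists would be a coherent sequence, and the robustness remark concerns the GLM alone. This is right, so *competing and unordered* is the fair description. The sequence is not written down.

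**The inflation is small and hypothetical.** A reader might take 6 to 7% as the plan's own error rate. It is the rate under free picking. A written gate (Kolmogorov-Smirnov in either group, then t or Mann-Whitney), simulated under the same distribution, gave 4.8 to 5.1%. This objection stands in full: the stronger ground is the unfixed estimand, not the inflation.

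**Two further inferences should be resisted.** One is to quote how often the normality test would detect the skew. That depends heavily on whether it is applied to pooled data, to each group or to residuals, and with or without the Lilliefors correction. The article does not say which, so no percentage is given here. The other is that a partial eta-squared of 0.14 serves as a significance threshold. The sentence "A partial Eta-squared measure will be used to compare the magnitude of changes with the large effect size, indicating a significant difference in magnitude" is loosely worded, but the text around it gives descriptive effect-size benchmarks and sets no such threshold.

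**An unseen analysis plan might settle this.** It could, but only by overriding what the article states. The defect is a stated rule that cannot be applied to the primary outcome, not a detail left for later.

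**Conclusion.** The point holds in this form. The method assigned to the intervention effect cannot be fitted to the primary outcome as written. The methods in the same section that can be fitted are not ordered for non-normal data and are gated on a normality p-value. As a result neither the primary test nor the quantity it estimates is fixed. That conclusion rests on the text alone: one LOS value per patient, an unrestricted GLM sentence, and two unranked instructions for skewed data.

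The size of the harm rests on an assumed lognormal LOS with SD 4.31 and control mean 8 to 12 days: type I error of about 6 to 7% instead of 5% under free choice, and differing significance verdicts in roughly 9 to 11% of trials if the planned difference is real. The inflation is modest. It should nevertheless be corrected before any group comparison, because it concerns the primary outcome and the correction is cheap.

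**What to change.** 1. Name one two-group analysis of LOS, adjusted for the stratification factors (BMI and gender), with its sidedness and a 95% CI. Two choices are sound. A linear model reporting the difference in days matches the sample-size basis. A linear model of log(LOS) reporting the geometric-mean ratio, with the difference in days alongside, handles skew better but makes the headline result a ratio. Either will do; one must be chosen.
2. Keep Mann-Whitney as the sensitivity analysis.
3. For LOS, remove the Kolmogorov-Smirnov gate, the logistic regression option and the reference to changes.
4. Limit the repeated-measures GLM, in the Abstract and in Analysis of results, to outcomes measured at two or more visits.
5. Optionally, reword the partial eta-squared sentence so that it describes effect size only.

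The cost is wording; no new data are needed. Timing matters: Trial status says recruitment was completed on 31 December 2021, and the article does not say whether LOS has been compared by group. The choice should be dated. If group results have already been seen, the report should say so and show LOS under each method that the article lists and that can be run.

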**Methods:**

This is a pragmatic randomized control trial study where elective admitted patients will be randomly divided into the intervention (SS) or control (NN) group. All data will be collected during a face-to-face interview, anthropometric measurement, blood sampling (albumin, white blood count, hemoglobin, and c-reactive protein), handgrip strength, and postoperative complications. Group SS will be receiving a tailored lifestyle and intensively supplemented with oral nutrition support as compared to Group NN that will receive standard medical care. The primary outcome *for this study is* the length of stay in the hospital. Additional outcome measures are changes in biochemical profile and nutritional and functional status. The effects of intervention between groups on the outcome parameters will be analyzed by using the SPSS General Linear Model (GLM) for the repeated measure procedure.

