**Biochemical data**				
Serum albumin—Medical report	/			/
White blood count—Medical report	/			/
Hemoglobin—Medical report	/			/
C-reactive protein	/			/

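### The repeated-measures GLM for the secondary outcomes names no tested term and does not take the pre-treatment baseline out of the time factor; a baseline-adjusted ANCOVA would be better

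*Protocol article*

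**What the plan says.** Under Analysis of results, the article states: "The effect of intervention between treatment groups on outcome parameters will be carried out by using General Linear Model (GLM) for repeated measure procedure". The abstract's Methods paragraph names the same SPSS procedure and likewise speaks of effects between groups. Neither place names a term of the model or says how the baseline value enters it.

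The primary outcome, length of stay, is one value per patient, so a repeated-measures model can only serve the secondary outcomes. The abstract describes these as follows: "Additional outcome measures are changes in biochemical profile and nutritional and functional status". The effect measure attached to the analysis also refers to change: "A partial Eta-squared measure will be used to compare the magnitude of changes with the large effect size". ANCOVA is mentioned once, for predictors of length of stay.

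The number of time points differs by outcome (Data collection procedure and Table 3):

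- Biochemistry has two: "biochemical data will be collected for a second time at the end of the study which is during visit 3".
- PG-SGA, weight, mid-arm circumference and skinfold have three. The text says "the same methods and instruments will be used repeatedly at visit 1 and visit 3", while Table 3 marks visits 2 and 3. Either way there is a baseline and two later values.
- Handgrip has four, since it is taken at every visit.

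The supplement is started at recruitment, so the baseline value precedes treatment.

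**The concern.** A repeated-measures GLM prints several tests. The between-subjects group test compares patient averages over all levels of time. If baseline is one of those levels, the average includes a visit at which randomisation makes the expected group difference zero. The hypothesis tested is then that the arms have equal means over baseline and follow-up together. That is not the hypothesis that the arms change equally, or that they are equal at follow-up given baseline. The group-by-time test does address change, but with two time points it is a change-score comparison, which uses the baseline less efficiently than ANCOVA does.

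Because the text names no term, two analysts could follow it and reach different conclusions from the same data. A real nutritional or functional benefit could be missed, or its size understated.

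**Working it through.** **Inputs from the article (Sample size calculation).** Effect size 0.8 (stated for length of stay), power 90%, alpha 0.05, drop-out 20%, 34 per arm.

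**The article's own figure.** n per arm = 2(z_alpha + z_beta)²/d².

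- One-sided: 2(1.645 + 1.282)²/0.64 = 26.8, so 27; 27/0.8 = 33.75, so 34 per arm and 68 in total.
- Two-sided t test: also 34 per arm, but before any drop-out allowance.

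The figure of 34 is therefore reproduced. I use 34 per arm, and 27 per arm for 20% drop-out.

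**Assumptions not in the article.** The 0.8 SD effect is carried over to the secondary outcomes. It is constant over the k post-baseline visits and zero at baseline. Variances are equal, every pair of visits has the same correlation rho, and tests are two-sided at 5%.

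**Dilution.** With T = k + 1 time points, the expected difference in patient averages is k/T of the true effect: 1/2, 2/3 and 3/4 for T = 2, 3 and 4. This does not depend on rho.

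**Standardised effects.**

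- Group main effect: d(k/T)/√((1 + (T−1)rho)/T)
- Group-by-time with T = 2 (change score): d/√(2(1−rho))
- Group-by-time with T > 2: F test with noncentrality (n/2)d²(k/T)/(1−rho)
- ANCOVA at one follow-up visit: d/√(1−rho²)

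The t-test noncentrality is the standardised effect times √(n/2), and √17 = 4.123 at 34 per arm. At rho = 0.5:

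- Main effect, T = 2: 0.4/√0.75 = 0.462; noncentrality 1.90; power 47%
- Main effect, T = 3: 0.533/√0.667 = 0.653; noncentrality 2.69; power 76%
- Main effect, T = 4: 0.6/√0.625 = 0.759; noncentrality 3.13; power 87%
- Change score, T = 2: 0.8/√1 = 0.8; noncentrality 3.30; power 90%
- ANCOVA: 0.8/√0.75 = 0.924; noncentrality 3.81; power 96%

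A simulation of 10,000 trials at T = 2 and rho = 0.5 gave 46.9% for the main effect and 90.4% for group-by-time.

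**Biochemistry (T = 2), power over rho.**

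| per arm | rho | group main effect | group-by-time | ANCOVA |
|---|---|---|---|---|
| 34 | 0.3 | 52% | 78% | 93% |
| 34 | 0.5 | 47% | 90% | 96% |
| 34 | 0.7 | 42% | 99% | 99.5% |
| 27 | 0.5 | 38% | 82% | 92% |

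**Three and four time points, 34 per arm.**

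| outcome | rho | group main effect | group-by-time | ANCOVA, last visit |
|---|---|---|---|---|
| PG-SGA, anthropometry | 0.3 | 84% | 82% | 93% |
| PG-SGA, anthropometry | 0.5 | 76% | 93% | 96% |
| Handgrip | 0.3 | 94% | 82% | 93% |
| Handgrip | 0.5 | 87% | 93% | 96% |

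For handgrip at rho = 0.3, averaging three post-baseline values offsets the dilution, and nothing is lost against a single-visit ANCOVA.

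**Effect on the reported magnitude.** For two equal groups, partial eta-squared is roughly D²/(D² + 4), where D is the standardised effect. For biochemistry at rho = 0.5, the same true effect gives 0.213/4.213 = 0.05 from the main effect, 0.64/4.64 = 0.138 from group-by-time and 0.853/4.853 = 0.18 from ANCOVA. Against the article's cut-offs (0.01, 0.06, 0.14) these read as small, just under large, and large.

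**The case against.** The strongest reply is that the article names a procedure and not a term. Speaking of an effect between treatment groups is ordinary prose for comparing arms. The references to changes, in the abstract and beside partial eta-squared, fit group-by-time at least as well as the group main effect. A statistical analysis plan that is not shown may settle the term. Group-by-time is valid, and at correlation 0.7 ANCOVA gains almost nothing over it. Analysis of results also mentions an ANOVA of values between groups. Applied to follow-up values, that would be undiluted, with about 90% power at 34 per arm.

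Most of this stands. A reader might infer that the plan prescribes the diluted test and so halves the power for all the secondary outcomes. The documents do not support that: no term is fixed, and the halving is confined to the two-time-point biochemistry. A much larger handgrip loss appears only if the supplement is assumed to have no effect at visit 1. The article gives no ground for that, since supplementation begins at recruitment.

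The reply does not remove the point. The procedure is stated in two places, nothing takes baseline out of the time factor, and under either reading a better analysis of the two-time-point outcomes is available from data already collected.

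**Conclusion.** The point holds as a low-cost improvement to a stated method. It is not an error that invalidates the analysis. Under the main-effect reading, the tested difference is 1/2, 2/3 or 3/4 of a constant post-baseline effect. Power at correlation 0.5 is then about 47% (biochemistry), 76% (PG-SGA and anthropometry) and 87% (handgrip). Under the group-by-time reading, the loss against ANCOVA for biochemistry is about 15 points at correlation 0.3, 6 at 0.5 and under 1 at 0.7; with 27 per arm it is about 10 points at 0.5.

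The power figures rest on a 0.8 SD effect that the article states only for length of stay, and on correlations that it does not give. The dilution fractions need only a constant effect after baseline. Type I error is unaffected under every reading, and only secondary outcomes are concerned. Dietary intake is left out, because its baseline is a one-day recall and its later values are two-day records.

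**What to change.** In the abstract's Methods and under Analysis of results, replace the GLM sentence with wording to this effect:

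*For each secondary outcome measured by the same method at baseline and later, the intervention effect is the between-group difference at a named follow-up visit, from an ANCOVA with the outcome's own baseline value as covariate. Where there are several follow-up visits, a repeated-measures model of the post-baseline visits with baseline as covariate is used, and the group contrast at the named visit is reported. Baseline is not a level of the time factor, and the between-subjects main effect over all visits is not used as the intervention effect.*

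Before naming the visit for PG-SGA and anthropometry, reconcile the text (visits 1 and 3) with Table 3 (visits 2 and 3).

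The cost is about one degree of freedom per outcome. No new data are needed, and SPSS fits these models. Trial status gives recruitment as completed on 31 December 2021, so the change should be dated and its timing relative to any look at the data recorded.
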